## Abstract

MS clinical features vary between patients. In approximately 60% of cases, cognitive deficits are associated with motor disabilities, with consequences on both walking and maintaining balance and cognitive efficiency. Multimodal programs are very infrequent for MS patients and cognitive rehabilitation is not provided by the Italian health system, which only favors access to motor rehabilitation. Dual-task studies showed how motor and cognitive skills are closely associated. Therefore, physiotherapy exercises may favor an indirect improvement in cognition. The aim of this study is to understand which rehabilitative approach may increase both cognitive and motor efficiency, avoiding the waste of time and resources. In this multi-site single-blind parallel controlled clinical trial, we will compare three rehabilitative approaches: cognitive training, motor training and combined cognitive–motor training. We also aim to evaluate: whether self-perception and objective improvement correspond; the impact of each rehabilitation program on patients’ QoL, mood and self-perception; and long-term effects. A total of 60 patients will be randomly assigned to one of the three treatments for two 45-min sessions/week for 12 weeks. All participants will undergo a complete cognitive, motor, clinical assessment together with mood, self-perception, and QoL questionnaires before, immediately after and 6 months after the training period.

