For the 12 weeks following randomization, each patient will undergo one of three rehabilitation programs:Reha 1: is composed by a computerized cognitive rehabilitation training using four sessions of the verbal memory set of the RehaCom program [15,16,17,18,19,20,21,22,23]. Each patient will carry out two 45-min sessions/week for 12 weeks;Reha 2: is composed by a combined rehabilitation program with the use of the four verbal memory sessions of RehaCom together with a motor rehabilitation program. Each patient will carry out one 45-min session of cognitive rehabilitation and one 45-min session of motor rehabilitation each week for 12 weeks;Reha 3: is composed of two 45-min sessions of motor rehabilitation training each week for a total duration of 12 weeks.

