### 4.2. Outcomes

The primary outcomes of this study are the scores on the cognitive tasks and the scores on the gait and balance efficiency scales.

The secondary outcomes are the scores on the self-perception of cognitive deficits scale and on the self-perceived quality of life through the WHO-DAS.

The outcomes will be considered at T1 and T2.

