## 6. Discussion

The present study will have the benefit of comparing three rehabilitation training sessions with a specific focus on cognitive outcomes. To date, the possible option for the management of cognitive dysfunctions in MS is CR, applied separately or as a part of a multimodal program involving also MR. However, in clinical practice, multimodal programs are very infrequent and patients with MS are primarily treated via pharmacological approach and subsequently via motor exercise training (physiotherapy). CR still remains poorly accessible for MS patients.

On the other hand, dual-task studies have shown how motor and cognitive skills are closely associated [57,58]. For example, during the execution of specific motor exercises, the subject automatically activates the processes of planning, control and coordination (executive functions) which, in turn, we know are connected to memory functions. It is, therefore, possible that physiotherapy exercises favor an improvement in memory performance indirectly, by strengthening the executive functions associated with memory. In fact, the SNC should not be thought of as a set of independent modules, but as a network or a set of networks closely linked to each other. The brain areas are richly connected from an anatomical and functional point of view: therefore, by activating, for example, the motor cortex with physiotherapy exercises, it cannot be excluded that neuronal activity in the involved brain areas may indirectly enhance memory functioning. Therefore, we should consider motor and cognitive skills only apparently independent.

In this regard, one study reported significant memory improvements and concomitant increases in hippocampal volume following aerobic training in two people with MS and memory impairment [59]. On the other hand, the execution of specific memory exercises could reduce motor disabilities by the indirect action on the relative brain circuits.

As a consequence, we could expect that the combined rehabilitation (Reha 2) would allow a double advantage (both at a cognitive and motor level), thus ensuring greater effectiveness for the patient and a lower amount of time and resources.

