Therefore, through this study, we aim to verify the hypothesis according to which combined rehabilitation intervention may be the best strategy to be used in MS patients having both motor and cognitive disabilities. We expect that a combined rehabilitation approach can bring a wider advantage as it may allow the enhancement of motor and cognitive skills at the same time.

Finally, by comparing the three rehabilitation approaches, we could even expect to highlight how the combined rehabilitation intervention favors an improvement in memory performance even higher than the CR alone.

If these results are reached, a change in clinical practice could be suggested: the combination of the two approaches in the same training with a reduction in time and costs for national health systems and a double advantage for MS patients.

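### The expected saving in time and costs from the combined programme cannot follow from any result of this trial: all arms get the same 18 hours, no resource use is measured, and no arm gets both full programmes

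*Protocol article*

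**What the plan says.** Three places in the protocol article raise saving of time or resources.

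- The Abstract describes the aim as finding an approach that helps both cognition and motor function, "avoiding the waste of time and resources".
- Section 6 expects Reha 2 to bring a cognitive and a motor benefit, "thus ensuring greater effectiveness for the patient and a lower amount of time and resources".
- The end of section 6 is conditional: "If these results are reached, a change in clinical practice could be suggested". The change is to combine the two approaches in one training, "with a reduction in time and costs for national health systems".

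On contact time, the Abstract has every patient "randomly assigned to one of the three treatments for two 45-min sessions/week for 12 weeks". Section 2.1 gives the detail. For Reha 1 (cognitive): "Each patient will carry out two 45-min sessions/week for 12 weeks". For Reha 2 (combined): "Each patient will carry out one 45-min session of cognitive rehabilitation and one 45-min session of motor rehabilitation each week for 12 weeks". Reha 3 is two 45-minute motor sessions a week over the same 12 weeks.

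On outcomes, section 4.2 begins "The primary outcomes of this study are the scores on the cognitive tasks" and adds the gait and balance scales. The secondary outcomes are self-perceived cognitive deficit and the WHO-DAS. In section 4.1, the between-group analysis names cognitive scores, anxiety and depression, self-perceived cognitive difficulty and perceived disability.

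**The concern.** A reduction in time and costs is a claim about resources. It needs either arms that differ in resources used or a measurement of those resources, and it needs the comparator against which the saving is counted. The design has none of these.

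At stake is the recommendation that the article links to success. The randomised comparison of clinical scores is unaffected. A favourable result, however, could be reported to health services as a demonstrated saving when the trial can only show which programme did more in the same number of hours.

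**Working it through.** **Inputs.** Sessions per week, session length and duration are from section 2.1 and agree with the Abstract. Outcomes are from section 4.2, assessments from section 2.3, and analyses and group size (20 per group, minimum 16) from section 4.1.

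**Step 1: contact time.** Minutes = sessions per week × 45 × 12.

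| Programme | Cognitive | Motor | Total | Sessions |
|---|---|---|---|---|
| Reha 1 | 2 × 45 × 12 = 1080 | 0 | 1080 min (18 h) | 24 |
| Reha 2 | 1 × 45 × 12 = 540 | 1 × 45 × 12 = 540 | 1080 min (18 h) | 24 |
| Reha 3 | 0 | 2 × 45 × 12 = 1080 | 1080 min (18 h) | 24 |
| Both in full (not an arm) | 1080 | 1080 | 2160 min (36 h) | 48 |

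Reha 2 minus Reha 1 = 0 min, and Reha 2 minus Reha 3 = 0 min. Reha 2 would save 2160 − 1080 = 1080 min only against the last row.

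**Step 2: resource measurement.** The assessments are clinical history, EDSS, the cognitive battery, mood and anxiety scales, WHO-DAS, MSNQ, MSFC, 6MWT, Tinetti and Berg. None records cost, staff time or use of services, so no cost difference can be estimated.

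**Step 3: what the hoped-for result would show.** Suppose Reha 2 is significantly better than Reha 1 on memory. Both used 18 h, so the finding is more memory benefit per hour. Time saved remains zero.

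**Step 4: what a saving against separate delivery would need.** Reha 2 contains half of each single programme (540 of 1080 min). The 18 h against 36 h argument needs both halves to hold their effect:

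- *Memory.* If Reha 2 beats full Reha 1, half the cognitive sessions plus motor work has done at least as well as the full cognitive programme. A test for a difference is enough here.
- *Gait and balance.* The matching contrast is Reha 2 minus Reha 3. Section 4.2 makes these scores primary, but the between-group list in section 4.1 does not name them.
- *Both together.* Whether Reha 2 matches a patient given both full programmes cannot be observed, because no arm receives them.

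**Step 5: precision of the missing contrast.** For an unadjusted difference between two arms, in SD units, with the error variance pooled over three arms, the 95% half-width is t × √(2/n).

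- n = 20: 2.002 × √(2/20) = 0.633 SD.
- n = 16: 2.014 × √(2/16) = 0.712 SD.

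Baseline adjustment would narrow these. The contrast can be estimated from data already collected, but coarsely, which is why the interval should be shown.

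The stated sample size plays no part in this argument.

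**The case against.** The strongest reply has three parts.

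1. *The sentence is hedged and sits in the Discussion.* It is not among the objectives in section 2.1, the outcomes or the analyses. This stands: it is a conditional expectation, not a pre-specified test. The same idea does appear in the Abstract's aim and twice in section 6, and it fails even when its condition is met.

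2. *The natural meaning is a saving against giving both programmes separately, and superiority on memory would settle the memory side.* This also stands. It leaves the motor side and the absent comparator, and a memory result fills neither gap.

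3. *The double advantage means benefit in two domains rather than one.* On that reading the relevant contrasts include Reha 2 minus Reha 3 on memory and Reha 2 minus Reha 1 on gait and balance. That is a fair reading, so the fix asks for both contrasts in both domains.

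A reader might go further and infer that a non-significant difference would be taken as the same benefit in less time. The documents do not say so: the results that trigger the practice change are superiority results, and a null result does not meet that condition. The supporting figure is also fragile. With 20 per arm, a true 0.5 SD deficit in Reha 2 would be non-significant at p < 0.016 in about 81% of trials, but only for an unadjusted comparison. With baseline adjustment it is about 60% at an assumed correlation of 0.7 and about 44% at 0.8, and the 0.5 SD is itself an assumption. This is a possible misreading to guard against, not something the plan proposes.

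Finally, a fuller analysis plan may name gait and balance. The article's own list of between-group variables is explicit, however, and does not match its primary outcomes.

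**Conclusion.** The point holds in a limited form. The difference in contact time between arms is exactly 0 min, no resource use is measured, and the only comparator that would yield a saving (36 h against 18 h) is not in the trial. A reduction in time and costs therefore cannot follow from any result, including the most favourable one. The trial can still answer which programme gives more benefit in 18 h.

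This rests on the session figures as written. It also assumes that separate delivery means each single programme given in full, one in addition to the other. No assumption about effect size or correlation is needed. The clinical comparison stands; the health-system conclusion and the missing motor contrast need correction.

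**What to change.** 1. In the Abstract and section 6, limit the aim and conclusion to which programme gives more benefit at equal contact time (18 h). Remove the reduction in time and costs, or label it a hypothesis that this trial does not test.
2. In section 4.1, add the gait and balance scores to the between-group analysis, so that it covers all primary outcomes.
3. Report estimates with 95% intervals for Reha 2 minus Reha 1 and Reha 2 minus Reha 3, on memory and on gait and balance, and base any double-advantage statement on these four contrasts. No margin is defined, so the intervals describe what the data allow and should not be presented as a demonstration of non-inferiority.
4. Add one sentence saying that a non-significant difference is not evidence of equal benefit.

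The cost is wording and a few more reported contrasts on data already collected. Arms, sample size and assessments are unchanged. The downside is a more modest health-system claim.

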## Figures and Tables

**Figure 1 neurosci-03-00029-f001:**
[figure not shown]
Study flowchart.

**Table 1 neurosci-03-00029-t001:** Inclusion and exclusion criteria for the enrollment of patients.

Inclusion Criteria	
**Diagnosis**	Diagnosis of MS defined according to McDonald’s diagnostic criteria revisited in 2011
**Age**	18–65 years
**Phenotype**	RRMS or SPMS
**Language**	Italian mother tongue
**EDSS**	<6.0
**Exlcusion Criteria**	
**Pathologies**	Neurological or psychiatric conditions other than MS that can interfere with cognitive functioning
**Neurological history**	Clinical relapses in the three months prior to enrollment, neurological pathologies other than MS and severe enough to interfere with cognitive functioning, and clinical relapse or disease activity highlighted on MRI magnetic during the treatment period
**Severe mental illness**	Psychiatric disorders severe enough to interfere with cognitive functioning
**Medications**	Steroid therapy in the 3 months prior to enrollment
**Motor limitations**	Dysfunction of the upper limbs (paralysis or tremor) that do not allow to hold the PC mouse
**Sensory limitations**	Visual acuity impaired enough not to allow reading of the instructions to the various tests

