## 2. Materials and Methods

### 2.1. Aim, Design and Setting of This Study

This study has the following primary objectives:Compare three forms of rehabilitation—cognitive, motor and combined (cognitive–motor)—in three groups of MS patients.Check whether a combined rehabilitation approach can induce a significantly greater improvement on memory efficiency of MS patients, than cognitive rehabilitation performed alone.

Secondary objectives:Evaluate whether self-perception and objective improvement correspond.Evaluate the impact of each rehabilitation program on patients’ overall disability.Monitor the effects of the three rehabilitation conditions after 6 months.

This study will be a single-blind parallel controlled clinical trial, in which each subject will be randomly assigned to a single treatment. The study protocol will be divided into an initial evaluation by standardized tools of clinical, cognitive, emotional, quality of life and functional self-perception state, at time 0 (T0). Subsequently, patients will be assigned to one of the three conditions and will undergo rehabilitation treatment for a total of 12 weeks (two sessions each week). At the end of the treatment, each patient will undergo an overall re-evaluation (T1) with parallel forms of the tools used at T0. After 6 months, all patients will be submitted to a further overall re-evaluation as a follow-up measurement of each treatment (T2). The examiner carrying out pre- and post-treatment evaluations will be different from the one carrying out the rehabilitation process in order to avoid any individual bias. Figure 1 shows the study flowchart.

Patients in charge of both the “Santa Lucia” Neuroscience and Rehabilitation Foundation (Rome) and the “Filippo Turati” Foundation (Rome) will be recruited. All evaluations and rehabilitation training will be conducted at the laboratory and in the rehabilitation sites of the two centers by adequately trained neurologists/physiatrists, psychologists and physiotherapists.

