
### 2.4. Randomization

After having completed the assessment procedures, the participants will be randomized to the three rehabilitation arms. The randomization assignment will foresee a stratification by age groups (<30; 30–40; 41–50; 51–65; >65) and will be weighted with respect to the variable phenotype of pathology (each group will be guaranteed a distribution of patients in RR or SP course representative of the incidence of the two courses in the Italian MS population) [55]. This will be a single-blind study.

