## 4. Statistics and Outcome

### 4.1. Data Analysis

The sample size has been determined based on an a priori power analysis, using the software G*Power 3.1 [56], with a 0.30 effect size, power of over 0.95, and an alpha level of 0.05, as being sufficient for both repeated measures, within–between interaction Analysis of Variance (ANOVA). The minimum number of participants required is 48 (16 participants for each group), but we have decided to reach a total number of 60 participants (20 participants for each group) in order to avoid possible drop-out effects.

For the purposes of this study, different types of statistical analysis will be carried out using SPSS 18 (SPSS Inc., Chicago, IL, USA) and a significant threshold throughout this study will be set at *p* < 0.05.

Statistical analysis will be of two types:“Within-group” analyses. These statistical analyses will be aimed at evaluating any improvement in patients’ cognitive performance. Within each group of patients, the assessments at T0 will be compared with that at T1 and T2 through a repeated measures ANOVA between the scores of the cognitive assessments. In case of significance, post hoc tests will be carried out to which a Bonferroni correction will be applied with significance set at *p* < 0.016. Similarly, the same analysis will be conducted to compare the levels of anxiety and depression, the self-perception of cognitive deficit and the level of perceived disability.“Between-group” analyses. These statistical analyses will be aimed at comparing the results obtained by the groups at T0, T1, and T2 by performing an ANOVA between the scores of the cognitive assessments. In case of significance, post hoc tests will be performed to which a Bonferroni correction will be applied with significance set at *p* < 0.016. Additionally, in this case, the same comparative analysis will be carried out on the following variables: levels of anxiety and depression, self-perception of one’s cognitive difficulties and level of perceived disability.

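### Table 1 excludes patients for a relapse or MRI activity during treatment, which can occur only after randomisation and which conflicts with re-evaluating all patients

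*Protocol article*

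**What the plan says.** Table 1 carries the caption "Inclusion and exclusion criteria for the enrollment of patients". Under neurological history it lists, beside relapses in the three months before enrolment, "clinical relapse or disease activity highlighted on MRI magnetic during the treatment period".

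The order of events is fixed elsewhere in the article:

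- Section 2.2 makes meeting the criteria a condition for being assigned to a programme.
- Section 2.4: "After having completed the assessment procedures, the participants will be randomized to the three rehabilitation arms".
- Section 2.1: "For the 12 weeks following randomization, each patient will undergo one of three rehabilitation programs".
- Section 2.1 then has each patient re-evaluated at T1, at the end of treatment, and says of T2: "After 6 months, all patients will be submitted to a further overall re-evaluation as a follow-up measurement of each treatment (T2".

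Section 4.2 names the cognitive scores and the gait and balance scores as primary outcomes, considered at T1 and T2. Section 4.1 raises the sample from 48 to 60 "in order to avoid possible drop-out effects". It says nothing about patients who meet the on-treatment criterion.

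**The concern.** An eligibility criterion should be decidable before allocation. This one is not: it describes something that happens to a patient already assigned to an arm and in training. Applying it selects the patients compared on an event after randomisation, and a relapse can itself change memory, walking and balance scores.

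If the selection works differently in the three arms, the difference between arms mixes the training effect with the effect of who was removed. Even if it works equally, the result describes only patients who stayed stable, which is narrower than the population randomised.

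The MRI part adds a difficulty. No MRI is among the T0 assessments listed in section 2.3, and section 2.1 says that T1 uses parallel forms of the T0 tools. On the article's text, exclusion for MRI activity may therefore depend on who happens to be scanned.

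**Working it through.** **1. Timing, with the passages side by side.** T0 assessment, then randomisation (2.4), then 12 weeks of treatment (2.1), then T1, then T2 six months later. The criterion refers to the treatment period, so it applies only after randomisation. Table 1 excludes such a patient, while section 2.1 re-evaluates each patient at T1 and all patients at T2. Both cannot hold as written unless exclusion means something short of leaving follow-up, and the article does not say so.

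**2. The plan's own numbers.** Section 4.1 sizes the trial "with a 0.30 effect size, power of over 0.95, and an alpha level of 0.05" for a within–between interaction in a repeated-measures ANOVA. The number of measurements and their correlation are not stated. Assume m = 2 measurements, correlation 0.5, sphericity 1 and k = 3 groups:

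- λ = N·m·f²/(1 − ρ) = 48 × 2 × 0.09/0.5 = 17.28, with 2 and 45 degrees of freedom.
- Power is 0.958, and 48 is the smallest multiple of three that reaches 0.95. The stated 48 is reproduced.
- 48/(1 − 0.20) = 60, so the reserve is 12 patients, or 20%.

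**3. How many patients could be affected.** The article gives no relapse rate. Assume 0.2 to 0.5 relapses per year and P(relapse in 12 weeks) = 1 − exp(−rate × 12/52):

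- Rate 0.2: 4.5%, or 2.7 of 60.
- Rate 0.5: 10.9%, or 6.5 of 60.

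That is about 3 to 7 patients, leaving 57 to 53 before MRI-only exclusions and other losses. This is above 48, so relapse alone does not threaten power.

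**4. Shift in one arm's mean.** Take 20 patients, of whom 2 fell by 1 SD and 18 are unchanged on average. The mean change is −2/20 = −0.1 SD with them and 0 without them: a shift of 0.1 SD. The standard error of a two-arm difference with 20 per arm is √(2/20) = 0.32 SD (taking the outcome SD as 1), so the shift is about a third of a standard error.

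**5. Bias if exclusion differs systematically by arm (illustration only).** Assume no direct arm effect, outcome SD 1, and correlation 0.25 between a latent tendency to remain relapse-free and the outcome. If a proportion p is excluded, the mean of those retained is 0.25·φ(z)/(1 − p), where z is the p-quantile of the standard normal. The difference is the first arm minus the second. The last column supposes that a relapse also lowers the score by 1 SD.

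| Excluded, first v second arm | Means of those retained | Difference after exclusion | Difference, all randomised, relapse costs 1 SD |
|---|---|---|---|
| 10% v 10% | 0.049 v 0.049 | 0 | 0 |
| 11% v 4.5% | 0.053 v 0.025 | +0.03 SD | −0.065 SD |
| 20% v 5% | 0.087 v 0.027 | +0.06 SD | −0.15 SD |
| 30% v 10% | 0.124 v 0.049 | +0.08 SD | −0.20 SD |

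Equal exclusion gives no bias. Unequal exclusion favours the arm that lost more patients and, when relapse lowers scores, can reverse the sign. A simulation of rows 1, 3 and 4 gave the same figures to two decimals. The splits are assumptions, and those in the last two rows reach well above the range in step 3.

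**The case against.** The strongest reply is that nothing in the article says these patients leave the analysis. Exclusion might mean stopping the training only. Section 2.1 speaks of re-evaluating everyone, and analysis sets are often defined in a full protocol or SAP that is not shown. It is right that removal from the analysis is the natural reading and not an explicit one. The criterion itself, however, is stated and not merely left out. If the sponsor means to keep these patients, Table 1 misstates the plan.

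The MRI point can be answered in part: section 2.3 is a list of T0 assessments, the flowchart is not visible here, and scanning may be described elsewhere. The MRI point therefore holds only as a possibility on the article's text.

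The reply on size also stands. Differential exclusion is not documented, a purely chance imbalance is noise and not systematic bias, and the 0.1 SD example is small beside the standard error.

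Two stronger readings are not supported:

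- A reader might infer that the planned ANOVA also drops anyone missing a visit. Section 4.1 is silent on missing data and puts the repeated-measures ANOVA under the within-group analyses. The arms are compared by a separate between-group ANOVA at T0, T1 and T2. Run visit by visit, that analysis would keep a patient who has T1 but not T2.
- A reader might infer that relapses are more likely to be noticed in Reha 3 because of more staff contact. Section 2.1 gives all three arms two 45-minute sessions a week.

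**Conclusion.** The point holds. Table 1 states an exclusion that can take effect only after randomisation, on an event related to the primary outcomes, and it conflicts with the re-evaluation of all patients in section 2.1. This follows from the text and needs no assumed rate.

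The consequence is conditional. If exclusion means removal from the comparison, and if relapse, MRI activity or their detection differ by arm, the comparison is biased. Its size cannot be derived from the article. Under the assumptions shown it runs from zero with equal exclusion to several hundredths of an SD when exclusion differs, and more when measured against the all-randomised difference. It would go too far to conclude that the arms are certainly no longer comparable. The extra 12 patients cover the lost numbers but do nothing for comparability.

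**What to change.** - In Table 1, limit the relapse and MRI criterion to events before randomisation.
- Record relapse or MRI activity during the 12 weeks as an event, by arm, and state how MRI activity is ascertained.
- Assess these patients at T1 and T2 like everyone else, so that Table 1 and section 2.1 agree.
- In section 4.1, analyse all randomised patients in their assigned arm. A mixed model on all available scores would allow this when a visit is missing.
- Report the analysis without these patients only as a sensitivity analysis.

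The cost is wording in Table 1 and section 4.1, plus somewhat noisier scores from patients who relapsed. The change should be made prospectively, because T1 and T2 scores that are not collected cannot be recovered. Whether training continues after a relapse is a clinical matter and is not addressed here.
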